***Unexpected Adverse Drug Reaction***

*An adverse reaction, the nature or severity of which is not consistent with the applicable product information (Product Monograph – see Table 3 for expected adverse drug reactions).*

Adverse reactions outside the range or severity of those listed in Table 3 and judged to be related to the study medication will be considered unexpected adverse drug reactions. Medical officers, the Jinja pediatrician co-investigator may judge the likelihood that an adverse event is related to study medication and is outside the

expected spectrum of previously documented adverse drug reactions for the purposes of reporting.

***Serious Adverse Event or Serious Adverse Drug Reaction***

*A serious adverse event (experience) or reaction is any untoward medical occurrence that at any dose:*

- *results in death,*
- *is life-threatening,*
- *requires prolongation of existing hospitalisation, or*
- *results in persistent or significant disability/incapacity*

In this trial of critically ill children hospitalized with severe malaria, mortality is expected to occur in approximately 20% of participants who receive standard medical care[90].

Monitoring serious adverse events during the trial is therefore complicated by the fact that death is part of the natural progression of disease, even under conditions of optimal clinical care (Uganda standard of care). We propose to monitor mortality continuously to detect variations above the baseline expected mortality rate, to allow for early implementation of corrective actions, if required.

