#### **4.5 Expected duration of subject participation**

*Duration of study gas (iNO or room air placebo):* maximum 72 hours (may be discontinued earlier if patient recovers and no longer tolerates face mask)

*Expected total duration of hospitalization for severe malaria:* 5 to 7 days

*Follow-up (1st visit):* 14 days after admission

*Follow-up (2nd visit):* 6 months after admission

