### **8.1 Specification of safety parameters**

The following standard definitions are based on the International Committee on Harmonization Guideline on Clinical Safety Data Management.

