### **8.3 Procedures for eliciting reports of and for recording and reporting adverse event and intercurrent illnesses**

SAE forms will be made available to the DSMB, ethics boards and regulatory authority according to their requirements, which differ between each body. Accordingly, all SAEs will be reported to MUREC and the Uganda NDA as soon as possible, but within 15 days of the event. Unexpected SAEs will additionally be reported to the DSMB chairperson, MUREC, NDA, Jinja Hospital REB (as soon as possible, but within 15 days of the event). Fatal and life-threatening unexpected SAEs will be reported to the DSMB chairperson, MUREC, NDA, Jinja Hospital REB as soon as possible, but within at most 7 calendar days. Finally, SAEs that are unexpected, related or possibly related to the study intervention, and suggest an increase in risk to study participants or others will also be reported to the UHN REB (Toronto).

All SAEs that occur during hospitalization will be reported as described above.

Regarding SAEs that occur after hospital discharge, reports will be issued as described above for events occurring up to day 14 of the study (i.e., after hospital discharge, out to 14 days post-enrolment).

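### The SAE definition in 8.1 has no criterion for a new admission, so a readmission that is not fatal, life-threatening or disabling is not serious, although 8.3 extends SAE reporting to day 14.

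*Protocol*

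**What the plan says.** Section 8.1 of the protocol introduces its safety terms as standard definitions based on an ICH guideline. Under the heading for serious adverse events and reactions it gives four alternative criteria:

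- "results in death"
- "is life-threatening"
- "requires prolongation of existing hospitalisation"
- "results in persistent or significant disability/incapacity"

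The list ends there. It has no item for a new admission and no general item for other medically important events.

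Section 8.3 sets the reporting routes. All SAEs go to MUREC and the Uganda NDA within 15 days. Unexpected SAEs go in addition to the DSMB chairperson and the Jinja Hospital REB, also within 15 days. Unexpected SAEs that are fatal or life-threatening go to these bodies within 7 days. The section then covers the time after discharge: "Regarding SAEs that occur after hospital discharge, reports will be issued as described above for events occurring up to day 14 of the study". It explains this as 14 days after enrolment.

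Section 4.5 expects a hospital stay of 5 to 7 days and places the first follow-up visit 14 days after admission.

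**The concern.** The definition suits a child who is still in the ward, but the reporting period runs well past the expected discharge. Once the child is home, the third criterion cannot be met by the event that brings the child back, because there is no current stay to lengthen. A site that follows 8.1 to the letter would class such a readmission as non-serious unless one of the other three criteria applied.

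At stake is the completeness of safety reporting. Tolerability and safety are specific aim 3 in section 3. The protocol names a harm that could surface in this way: section 2.2 cites a meta-analysis linking iNO to renal dysfunction, and section 2.3 lists renal insufficiency among the adverse effects. The halting rules in sections 4.6 and 8.2 look at mortality only, so they would not pick up non-fatal readmissions.

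**Working it through.** No sample size, power or alpha figure is involved. The check compares the definition with the reporting rule and then looks for text elsewhere that closes the gap.

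**1. Length of the exposed window.** Inputs: SAE reporting to day 14 (8.3) and an expected stay of 5 to 7 days (4.5), taking enrolment as close to admission.

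- Stay of 7 days: 14 − 7 = 7 days after discharge; 7/14 = 50% of the period.
- Stay of 5 days: 14 − 5 = 9 days after discharge; 9/14 = 64% of the period.

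These are shares of calendar days, not of risk.

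**2. The criteria applied to one case.** Take a child discharged on day 6 and readmitted on day 10 with impaired kidney function that is not life-threatening and later resolves.

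| Criterion in 8.1 | Met? |
|---|---|
| Death | No |
| Life-threatening | No |
| Prolonged existing stay | No; the child was at home when the event began |
| Lasting or significant disability | No |

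The event is not serious as written. If the same event had occurred on day 5 and delayed discharge, it would have been serious.

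**3. Reports that follow under 8.3.**

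| Route | Readmission as 8.1 stands | If readmission were a criterion |
|---|---|---|
| All SAEs: MUREC and NDA, 15 days | No report | Report |
| Unexpected SAEs: also DSMB chairperson and Jinja REB, 15 days | No report | Report if unexpected |
| Unexpected fatal or life-threatening SAEs, 7 days | Already reported | No change |

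Table 3 in 8.1 does not list renal injury. If the example were judged related to study gas, 8.1 would treat it as an unexpected reaction, so the second row would apply to it.

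**4. Text elsewhere.** Section 4.9 speaks of severe adverse events including deaths and does not define seriousness further. Sections 8.2 and 8.3 use the term SAE without adding to it. The day-14 items named in section 4.9 are vital status and a blood sample for parasite density; readmission is not mentioned. None of these sections makes a new admission serious.

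**The case against.** A good deal can be said for the plan, and most of it stands.

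- **A reader might infer that 8.1 and 8.3 contradict each other.** They do not. Deaths, life-threatening events and lasting disability after discharge still qualify, and 8.3 works for them. The gap is a definition narrower than the period it serves.
- **A reader might infer that every readmission escapes.** Only those that meet none of the other three criteria do.
- **A reader might infer that the events disappear.** Any untoward occurrence is an adverse event, entered on the CRF and in a cumulative log with severity, causality and expectedness, and the log is reviewed periodically (4.9, 8.1, 8.2). Recrudescence at day 14 is a secondary endpoint with its own blood sample.
- **A reader might infer that the DSMB would lose sight of all such cases.** Only unexpected SAEs go individually to its chairperson, so a readmission judged expected would not take that route even after the change.
- **A reader might infer a biased comparison of SAEs between arms.** Section 9.1 describes no such comparison, so the documents do not support that claim.
- **Renal harm is watched during exposure.** Creatinine is measured at least daily, acute kidney injury ends study gas, and discontinuations count as adverse drug reactions. Gas lasts at most 72 hours (3 days), so the window opens at least 5 − 3 = 2 days after exposure ends when the stay is as expected.

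It may also be said that a sensible site would treat an early readmission as a continuation of the first stay. The text does not say so, and staff could differ. None of these points supplies the missing criterion.

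**Conclusion.** The point holds in a limited form. Section 8.1 states a closed rule, and that rule classes a readmission that is not fatal, life-threatening or disabling as non-serious during a period in which 8.3 intends SAEs to be reported. The loss is in classification and in the 15-day reports; the 7-day route loses nothing.

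The number affected cannot be estimated from the protocol. A reader might apply an assumed readmission rate to the survivors: with the expected mortality of 20%, 180 × 0.8 = 144 survive, and 2 to 10% of 144 is about 3 to 14. The documents give no such rate. The count would also include readmissions that are already serious on other grounds, so it is an upper bound even on its own assumption. It should not be read as the size of the defect.

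The conclusion rests only on the protocol's own sections 8.1 and 8.3. Whether the list departs from the ICH text that 8.1 names cannot be checked here and is not part of the argument. The primary Ang-2 analysis, the sample size, the mortality endpoints and the halting rules are unaffected. The change is worth making because it is cheap and closes a gap in safety capture.

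**What to change.** Widen the third criterion in section 8.1, for example to: *requires inpatient hospitalisation (other than the index admission) or prolongation of an existing stay*. Put the same wording on the SAE form. Add a question on readmission, with its date and reason, to the CRF for the day-14 visit that is already planned, so that admissions to other facilities are also found.

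The cost is one line in 8.1, the matching line on the SAE form, one added question at day 14 and a few more SAE reports. No visit or sample is added.

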**8.2 The methods and timing for assessing, recording, and analysing safety parameters**

Adverse events, ADRs, and SAEs will be monitored continuously during the trial by medical officers and/or dedicated nursing staff. They will be recorded on case report forms. In addition, a running log of adverse events will be kept and reviewed periodically to allow the study team to assess if any patterns of adverse events emerge in real time. Discontinuation of study gas treatment and/or withdrawal of study

treatment in any subject will require the completion of a form detailing the reason for study gas discontinuation/withdrawal. All study deaths will require completion of an SAE form, which will be made available to the DSMB, ethics boards and regulatory authority according to their requirements, as described in section 8.3 *Procedures for eliciting reports of and for recording and reporting adverse event and intercurrent illnesses*.

**Halting rules**

Halting rules temporarily suspend study enrollment until a safety review is convened.

The objective of this review will be to decide whether the study should continue per protocol, proceed with caution, be further investigated, be discontinued or be modified and then proceed.

Halting rules for this study will be:

1. Mortality in any sequential group of 10 patients above statistical upper control limit (6/10 patients = 60%).
2. Cumulative mortality in any of the arms of the trial in excess of the upper statistical threshold.

Justification for these statistical thresholds is given in Appendix 1.

Safety review, interpretation of results and decisions about discontinuation of the trial will be made by a Data and Safety Monitoring Board (DSMB), using the suggested guidelines given here. We do not propose that the DSMB be strictly bound by pre-specified criteria, because of the complexity of the trade-offs between safety, efficacy,

and costs, and the possibility that new information will change considerations. Rather, consideration of stopping guidelines requires a reasoned judgment based on all information that is available at the time of data review.

### **8.3 Procedures for eliciting reports of and for recording and reporting adverse event and intercurrent illnesses**

SAE forms will be made available to the DSMB, ethics boards and regulatory authority according to their requirements, which differ between each body. Accordingly, all SAEs will be reported to MUREC and the Uganda NDA as soon as possible, but within 15 days of the event. Unexpected SAEs will additionally be reported to the DSMB chairperson, MUREC, NDA, Jinja Hospital REB (as soon as possible, but within 15 days of the event). Fatal and life-threatening unexpected SAEs will be reported to the DSMB chairperson, MUREC, NDA, Jinja Hospital REB as soon as possible, but within at most 7 calendar days. Finally, SAEs that are unexpected, related or possibly related to the study intervention, and suggest an increase in risk to study participants or others will also be reported to the UHN REB (Toronto).

All SAEs that occur during hospitalization will be reported as described above.

Regarding SAEs that occur after hospital discharge, reports will be issued as described above for events occurring up to day 14 of the study (i.e., after hospital discharge, out to 14 days post-enrolment).

#### **8.4 The type and duration of the follow-up of subjects after adverse events**

If a subject is withdrawn because of an adverse event, the subject will be followed and treated by the medical officer until the abnormal parameter or symptom has resolved or stabilized.

The adverse events must be followed to resolution and the follow-up evaluations noted in Adverse Event CRF and recorded when the subject has stabilized.

### **9 STATISTICS**

#### **9.1 Description of statistical methods to be employed**

##### ***Primary outcome***

The primary focus is whether or not the rate of reduction in Ang-2 differs between the treatment groups. In statistical terms, this is a *time-by-treatment* interaction. Given that we will have repeated measurements, possibly incomplete, over time, a linear mixed-effect model will be used to estimate and test the magnitude of the *time-by-treatment* interaction. A linear time trend will not be assumed by treating “day” as a categorical variable in the model. Log transformation of the data may be considered, as appropriate.

The primary analysis will be by *intention-to-treat*. That is, patients will be analysed in the group to which they were randomized, regardless of the deviations from study protocol. A secondary *per-protocol* analysis may be considered if important deviations from protocol compromise the validity of the ITT analysis. Subgroup analyses related to important prognostic factors will be performed: age < 5 years or ≥5 years;

uncomplicated or severe malaria; HIV seropositivity; and bacterial co-infection (see below).

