## **4 TRIAL DESIGN**

### **4.1 Endpoints**

*Primary endpoint:* Daily rate of change of Ang-2

*Secondary endpoints:*

1. Clinical efficacy:
  - a. 48 hour and 14-day mortality
  - b. recovery times:
    - i. time to fever resolution
    - ii. time to sit unsupported
    - iii. time to hospital discharge
  - c. time to parasite clearance
  - d. incidence of recrudescence at day 14

2. Other biomarkers and genetic determinants of malaria disease severity
  - a. whole blood lactate level
  - b. biomarkers and genetic determinants of endothelial activation, inflammation and coagulopathy, to be determined
3. Neurocognitive outcome at 6 months after discharge

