***Primary outcome***

The daily change in Ang-2 over the hospital admission will be the primary efficacy outcome. Elevated Ang-2 levels are associated with poor clinical outcome in severe malaria[33, 34] and Ang-2 has been used to follow disease progression and recovery in previous studies of malaria[33]. Thus, Ang-2 is an objective, quantitative marker of disease severity, validated for longitudinal follow-up of patients with malaria. Ang-2 levels will be measured longitudinally at admission (day 0), day 1, day 2 and day 3 of hospital admission. In patients treated for severe malaria who survive the infection, Ang-2 levels have been shown to decrease linearly during recovery at a mean rate of 2700pg/mL per 24h[33].

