### **4.3 Description of measures taken to minimize bias**

#### **(a) Randomization**

##### ***Sequence generation***

A computer generated randomization list will be created. Simple randomization will be used. Important prognostic variables including patient age, disease severity, and HIV seropositivity will thus be expected to be distributed randomly between treatment arms.

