## **9.2 Number of subjects planned to be enrolled**

We will enrol 180 patients (approximately 90 in each treatment arm).

Based on a recent clinical trial of L-arginine as adjunctive treatment for severe malaria, among patients who subsequently recovered, Ang-2 decreased by 2700pg/mL/day (95%CI 1800-3600pg/mL/day)[33]. We assume that a 50% change in this parameter would represent a clinically significant therapeutic effect. By standard calculations for normally distributed data, 80 patients per group will provide 80% power to detect a difference between two treatment arms of 1350pg/mL/day at  $p=0.05$  (two-sided). This corresponds to a 50% difference in the rate of change of Ang-2 between the arms. To account for possible dropout, loss to follow-up, and/or non-evaluable data of 10% of patients, approximately 90 patients per study arm are required.

However, these calculations do not reflect the analytic plan. Therefore, a simulation study was performed. A number of assumptions needed to be made, such as within patient correlation and Ang-2 variability. Patient Ang-2 data were simulated using a

multivariate normal distribution. A simple autoregressive correlation structure was used with correlations of 0.75, 0.5 and 0.25 for lags 1, 2 and 3 respectively. In previous studies, variability appears proportional to the mean[33]. Simulations were run with three different relationships where the standard deviation was taken to be 40%, 50% and 80% of the Ang-2 mean at each time point. Both groups were assumed to start at Ang-2 levels of 15,000 pg/mL and the average values at each of days 1, 2 and 3 based on the hypothesized slopes of Ang-2. One thousand replications were performed at each standard deviation relationship and treatment effect. The mixed effects models were fit and the likelihood ratio test was used to test the hypothesis of no time by treatment interaction at the 5% level (two tailed). Table 4 shows the results of the power simulations.

Table 4: Power simulations for 90 patients per group

| Standard Deviation
(% of mean) | Slope Difference               |                                        |                                        |
|-------------------------------------------|---------------------------------------|----------------------------------------|----------------------------------------|

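### The primary Ang-2 test names no baseline constraint or covariate and leaves the log scale optional; under the protocol's own variance assumption this uses only a minority of the available information

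*Protocol*

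**What the plan says.** Section 4.1 gives the primary endpoint as one quantity: "Daily rate of change of Ang-2". The Primary outcome text under 4.1 schedules Ang-2 at "admission (day 0), day 1, day 2 and day 3 of hospital admission".

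Section 9.1 states that "a linear mixed-effect model will be used to estimate and test the magnitude of the" time-by-treatment interaction, with day entered "as a categorical variable in the model" so that a linear trend is not assumed. On scale it says only: "Log transformation of the data may be considered, as appropriate". It does not mention a baseline covariate or a common day-0 mean.

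Section 9.2 plans in pg/mL with a likelihood ratio test of the interaction and starts both arms at 15,000. It observes: "In previous studies, variability appears proportional to the mean". Section 4.3(a) says: "Simple randomization will be used".

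**The concern.** Three choices meet in this test.

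- **Baseline.** If day 0 is an outcome with its own group difference, the interaction compares unadjusted changes from baseline, and the noise in day 0 enters every comparison. Randomization gives both arms the same expected day-0 mean, so that noise need not be there. When SD is proportional to the mean, day 0 is the noisiest of the four days.
- **Scale.** SD proportional to the mean is the standard reason to analyse logs. Parallel raw profiles and parallel log profiles are different null hypotheses, so an optional log leaves the primary hypothesis open.
- **Contrast.** A 3-df interaction test has no direction and is not a daily rate, whereas the endpoint is a single rate.

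At stake is power at a fixed sample size. The possible sample size increase at the interim analysis (Section 9.2) is also affected, since an efficient test might not need it.

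**Working it through.** **Inputs (Section 9.2).** Day-0 mean 15,000 in both arms; control slope -2700 pg/mL/day; slope differences 810, 1080 and 1350; SD 40%, 50% or 80% of the mean at each day; correlations 0.75, 0.5 and 0.25 at lags 1, 2 and 3; 90 per arm; two-sided 5%.

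**Reproducing Table 4.** The simulation used a raw-scale, free-baseline, 3-df likelihood ratio test with a random intercept, iNO declining faster, and negative values set to 0 (an assumption; 6,000 runs):

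| SD | Table 4 (810/1080/1350) | Reproduced |
|---|---|---|
| 40% | 82/97/99 | 82/97/100 |
| 50% | 66/89/98 | 67/89/98 |
| 80% | 42/60/80 | 40/61/79 |

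All nine cells agree within 2 points, which supports the free-baseline reading. This random-intercept test has a simulated type I error of 7.5-7.7% under the planned covariance, so Table 4 is somewhat optimistic.

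**Where the information goes: day 3, SD 80%, difference 1350.** Day-0 SD is 12,000 in both arms. Day-3 means are 6,900 and 2,850, so the SDs are 5,520 and 2,280. The day-3 difference is 3 x 1350 = 4,050. Variances are in millions.
- Unadjusted change, control: 144.00 + 30.47 - 2(0.25)(12,000)(5,520) = 144.00 + 30.47 - 33.12 = 141.35. iNO: 144.00 + 5.20 - 13.68 = 135.52. SE = sqrt((141.35 + 135.52)/90) = 1.754, that is 1,754 pg/mL, so the difference is 4,050/1,754 = 2.31 SE.
- Adjusted for day 0, common regression slope (0.115 + 0.0475)/2 = 0.08125: residual variances are 28.73 and 5.04. SE = sqrt((28.73 + 5.04)/90) = 0.613, that is 613 pg/mL, so the difference is 4,050/613 = 6.61 SE.

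**All days, unstructured covariance, no flooring.** Let d be the vector of mean differences (zero at day 0), V = (S0 + S1)/90 with S0 and S1 the arm covariances, and C the matrix taking changes from day 0.
- Free baseline: L_free = (Cd)'(CVC')^-1(Cd).
- Common baseline: L_com = d'V^-1 d.
- Power is the chance that a noncentral chi-square on 3 df exceeds 7.81.

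SD 80%:

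| Case | Difference | L_free | L_com | Ratio | Power, free | Power, common |
|---|---|---|---|---|---|---|
| iNO faster | 810 | 2.27 | 15.02 | 6.6 | 21% | 92% |
| | 1080 | 4.08 | 29.60 | 7.3 | 37% | 100% |
| | 1350 | 6.41 | 50.23 | 7.8 | 55% | 100% |
| Other arm slower | 810 | 1.96 | 6.99 | 3.6 | 19% | 59% |
| | 1080 | 3.37 | 10.98 | 3.3 | 31% | 80% |
| | 1350 | 5.08 | 15.23 | 3.0 | 45% | 92% |

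The ratios are the same at SD 40% and 50%, because the SD factor cancels. The free baseline therefore uses 1/7.8 to 1/6.6 = 13-15% of the information, or 1/3.6 to 1/3.0 = 28-33% in the slower case. With values floored at 0, as in the reproduction, the common-baseline 3-df test gives 97/100/100% at SD 80% and 100% in every SD 40% and 50% cell.

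**How far this rests on the variance pattern.**
- Constant SD over days, raw scale: ratio 1.60, a loss of 1 - 1/1.60 = 37.5%.
- Log scale (log-normal with constant CV, substituted for the protocol's normal model): ratio 1.43-1.47, a loss of 30-32%. Here the free-baseline 3-df test already has 91/100/100% at SD 80% with iNO faster; a common baseline gives 98/100/100%.

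**Degrees of freedom.** With a free baseline, raw scale, SD 80% and iNO faster, a 1-df slope test gives 33/52/72% against 21/37/55% for 3 df. With a common baseline, moving to 1 df raises the first cell only from 92% to about 93%. In the slower case it moves 59/80/92% to 70/88/96%.

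**The case against.** The strongest reply is that the trial is adequately powered as planned. At the 1350 pg/mL/day design effect Table 4 states 99/98/80%, so a reader who infers that most of the power is thrown away goes too far. More than half of the power is lost in only one of the nine cells (SD 80%, 810). The large ratios also come from an assumed variance pattern, and the remedies overlap. All of this stands.

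Three further inferences are not supported:
- That the protocol forbids baseline adjustment. It is silent, and a separate analysis plan could supply it. The free baseline is inferred from that silence and from the reproduction of Table 4.
- That the scale will be picked after seeing results by arm. Section 9.1 gives no timing, and Section 4.8 has the analysis run under masked group labels.
- That the planned model cannot give a daily rate. The day-0-to-day-3 contrast divided by 3 is estimable from it, and categorical day deliberately avoids assuming linearity. What is missing is naming that contrast as primary.

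The log-scale figures also need a model other than the protocol's. Under its normal model with SD 80% of the mean, P(Z < -1.25) = 10.6% of values are negative and have no logarithm.

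None of this removes the core: the protocol's own assumptions favour using day 0, the sample is already planned, and Section 9.2 itself gives the reason for a log scale that Section 9.1 leaves optional.

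**Conclusion.** The point holds as an improvement that needs no extra patients or samples, not as a fault that invalidates the trial. If SD is proportional to the mean, as Section 9.2 assumes, the implied free-baseline test uses 13-15% of the available information when iNO declines faster and 28-33% when the other arm declines more slowly. In the faster case the SD 80% row would be about 92-97/100/100% with a common baseline. That compares with the stated 42/60/80%, or with 21/37/55% for a free-baseline test with unstructured covariance. At 1350 the gain over Table 4 is about 20 points at SD 80% and 1-2 points at SD 40-50%.

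If SD is constant, or on the log scale, the loss is about a third of the information. In the faster-decline case either the log scale or the baseline constraint alone recovers most of the loss. The 3-df choice costs least; its main weakness is the mismatch with a single-rate endpoint.

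These figures assume complete data and a day-0 sample drawn before study gas starts. Section 4.9 lists that sample with study-entry blood work but does not state the order.

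**What to change.** In Section 9.1, or in the analysis plan before unblinded data are seen:

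1. Keep the mixed model with day categorical, but constrain the day-0 means to be equal between arms, or adjust for day-0 Ang-2. State that the day-0 sample precedes study gas.
2. Fix the scale. Section 9.2 supports log Ang-2, with the raw pg/mL/day estimate as supportive.
3. Name one 1-df contrast as the primary estimate: the treatment difference in average daily change over days 0-3. Keep the 3-df interaction test as supportive.

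No additional child, visit or blood draw is needed. The cost is in restating the design: on the log scale the effect is a ratio per day, so the 1350 pg/mL/day effect and Table 4 would have to be re-expressed and re-simulated. Doing this in advance matters because Section 9.6 treats departures from the protocol's analyses as post hoc and exploratory.
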